**Methods/design:**

This is a parallel, two-arm, open, randomized controlled clinical trial with older people with knee OA. Volunteers will be allocated to an aquatic intervention group (WG), subjected to the intervention, or to a control group, not be subjected to any kind of intervention. Data collection pre- and postintervention will be composed of the evaluation of the perception of pain by visual analogue scale with application of nociceptive stimuli in four anatomical points of the knee, functional fitness tests, and application of the World Health Organization Quality of Life Scale abbreviated version and Western Ontario and McMaster Universities Osteoarthritis Index. The program will last 12 weeks, consisting of aerobic and functional exercises in the form of circuit training.

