Thus, the study will be divided into four moments: M_0_ (recruitment and screening), M_1_ to test and evaluative measures, and M_2_ and M_3_ for evaluation of the flexibility and reevaluation of tests and measurements (Fig. 1).

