### Analysis

The normality of the data will be verified with the Shapiro-Wilk test. Parametric data will expressed as mean and SD, using Student’s *t* test for independent samples to compare the groups and two paired samples to compare the times. For the analysis of repeated measures, analysis of variance with a post hoc Tukey test will be used. Nonparametric data will be expressed as median, maximum, and minimum values. The Mann-Whitney *U* test will be used to compare the groups, and for comparison of moments, the Wilcoxon test will be applied. In all tests, results will be judged to be statistically significant when α values are <0.05.

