## Discussion

The objective of this clinical trial is to evaluate the effect of aquatic physical therapy in older people with knee OA. The study is guided by practice-based scientific evidence for the use of aquatic rehabilitation exercises for this condition.

Upon completion of data collection, it is expected that the WG volunteers will benefit from increased flexibility through the Wells test, improved functional capacity through the TUG test, reductions in scores on the WOMAC, and quality of life assessed by the WHOQOL-BREF. In the CG, no changes in the values of any variable analyzed are expected. It is believed that the desired results could be attributed to physical and physiological effects of immersion in heated water associated with the proposed exercise protocol. The data will be published after the study is completed.

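### Flexibility appears to have three moments, yet the rank branch compares moments by Wilcoxon tests at 0.05 with no overall test or adjustment (within-arm family-wise error about 11–12%), and the parametric branch does not say which of its two methods applies

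*Protocol article*

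**What the plan says.** **Schedule (protocol article, Intervention and follow-up periods).** M0 is recruitment and screening. The section then gives "M_1_ to test and evaluative measures" and "M_2_ and M_3_ for evaluation of the flexibility and reevaluation of tests and measurements". The abstract (Methods/design) describes two occasions only: "Data collection pre- and postintervention will be composed of the evaluation of the perception of pain". Figures 1 and 2, which may set out the moments by outcome, are not shown in the text reviewed.

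**Analysis section.** A Shapiro-Wilk test decides the branch.
- Parametric branch: paired t tests compare times. In addition, "For the analysis of repeated measures, analysis of variance with a post hoc Tukey test will be used". The section does not say which outcomes get which.
- Non-parametric branch: Mann-Whitney compares groups, and "for comparison of moments, the Wilcoxon test will be applied".
- Both branches: "In all tests, results will be judged to be statistically significant when α values are <0.05".

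**Discussion.** The aquatic group (WG) is expected to benefit, with flexibility listed first. For the control group (CG): "In the CG, no changes in the values of any variable analyzed are expected".

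**The concern.** The Wilcoxon signed-rank test compares two occasions. An outcome with three occasions has three pairs. Testing each pair at 0.05, with no overall test first and no adjustment, lifts the chance of some false positive in an arm well above 5%.

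The parametric branch has a route that handles several moments (ANOVA with Tukey), and the rank branch has no counterpart. The same question about the same people can therefore carry a different error rate depending on a normality test run on 15 values per arm. Because the parametric branch also lists paired t tests without saying when they apply, it too could be run unadjusted on three moments.

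What is at stake is the reliability of statements such as flexibility having improved between two moments within an arm. These matter more than usual here. The Discussion describes the expected result arm by arm, and the Analysis section does not say that the conclusion rests on the between-group tests or that those tests compare change.

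**Working it through.** **Inputs**
- 15 per group (Sample size; Randomization and allocation).
- 0.05 for every test (Analysis).
- Three flexibility moments: inferred from the schedule section, not listed there.
- Number of pairs tested: not stated, so two cases are shown.
- Correlation and distribution over time: not stated, so a range is assumed.

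The plan states no family-wise error rate, so there is no figure of its own to reproduce.

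**Step 1: simple bounds for one arm, no true change**
- If the three tests were independent: 1 − 0.95³ = 0.143. For two tests: 1 − 0.95² = 0.098. These are too high, because the differences share moments.
- Large-sample value for three pairwise contrasts under equal correlation: the probability that the studentized range of three means exceeds 1.96 × √2 = 2.77, which is 0.122.

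**Step 2: exact Wilcoxon tests at n = 15**

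The two-sided exact test rejects when the smaller rank sum is 25 or less, a true level of 0.0479. Chance of at least one rejection, 50,000 simulated arms for each row:

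| Assumed data | All three pairs, Wilcoxon | M1–M2 and M1–M3 only, Wilcoxon | Three paired t tests |
|---|---|---|---|
| Normal, equal correlation | 12.2% | 9.0% | 12.5% |
| Lognormal | 12.3% | 9.0% | 9.2% |
| t, 3 df | 12.2% | 8.8% | 11.2% |
| Normal, AR(1), 0.7 | 11.5% | 8.1% | 11.9% |
| Normal, AR(1), 0.9 | 11.5% | 8.1% | 11.8% |

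A separate run with normal data and correlations of 0.5 to 0.9 gave 11.4–12.2% for all three pairs. Counting both arms, 1 − (1 − 0.122)² = 0.229, or about 23%.

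**Step 3: the ANOVA/Tukey route**

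Tukey comparisons on the repeated-measures residual (q = 3.499 with 3 means and 28 df) gave 4.8–6.4% over the correlation patterns tried, including AR-type correlation and standard deviations rising as 1, 1.2, 1.5. That is close to nominal.

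**Step 4: set the branches side by side**
- Rank branch: about 11–12%, or 8–9% with M1 comparisons only.
- Parametric branch, Tukey: about 5–6%.
- Parametric branch, unadjusted paired t on all three pairs: about 12.5% for normal data with equal correlation.

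**Step 5: effect of a remedy in the rank branch, n = 15, no true change**
- Wilcoxon tests at 0.05/3 each: 4.0–4.2%. When no moment differs, Holm makes at least one rejection exactly when this rule does, so the figure is the same.
- Friedman at 0.05 first, then the pairs: 4.1% (Friedman alone 4.8%). With three moments this order suffices: if the moments are not all equal, at most one pair can still be equal.

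**The case against.** The case on the other side has real force.

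- **Three moments is an inference.** The abstract speaks only of before and after, and the figures are not shown. This stands as a condition. If flexibility is measured twice, the multiplicity point falls away.
- **12% is the largest case.** It needs the rank branch and all three pairs. This stands, which is why the 8–9% figure is given beside it.
- **Multiplicity detail can be left to a fuller document.** This stands only in part. The article names a two-occasion test for comparing moments and sets 0.05 for all tests, so it states a rule. The threshold sentence does not forbid adjusted p-values, but nothing in the rank branch supplies any.
- **The randomised comparison is planned.** Independent t and Mann-Whitney tests compare the groups, and the ANOVA could include group. This stands. The inflation affects within-arm statements, and the remaining gap is that change is not named as what is compared.

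A reader might also infer three stronger points, which the document does not support.

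- **That the two parametric rules contradict each other.** They can be reconciled: paired t for two moments, ANOVA with Tukey for more. The fault is that they are unassigned.
- **That Tukey is invalid here and must go.** Run with an independent-groups error term, it would have family-wise error of at most 1.1%, and 4% power against 72% for a 0.5 SD change at correlation 0.8. But the article attaches Tukey to repeated measures and nowhere states that error term.
- **That success is defined as WG significant and CG not.** With the three Wilcoxon tests, that pattern would arise in about 11% of trials with no change in either arm (0.121 × 0.879 = 0.106), and in 23% if both arms improved equally by 0.3 SD at correlation 0.7 (0.362 × 0.638 = 0.231). The Discussion states an expectation, however, and adopts no such rule.

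**Conclusion.** The point holds in limited form. If flexibility is measured at M1, M2 and M3, the rank branch as written has a within-arm family-wise error of about 11–12% for all pairs, or about 8–9% for comparisons with M1. The parametric branch gives about 5–6% by Tukey, or about 12.5% if the paired t tests are used on all three pairs. So the error rate depends on the Shapiro-Wilk result when Tukey is the parametric method, and is inflated in both branches when it is not.

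These figures assume 15 analysed per arm and no true change. They varied little over the correlations and distributions tried, apart from the t tests on skewed data (9.2%). The point concerns one outcome and its within-arm statements. It does not show that the between-group tests are wrong, only that they are not tied to change or to the conclusion.

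**What to change.** 1. State which moments apply to each outcome, if the figures do not already do so.
2. For flexibility, fit one repeated-measures model with group, moment and group × moment. Draw the conclusion from the between-group difference in change from M1 to M3.
3. If within-arm comparisons are reported, label them descriptive and control multiplicity in both branches:
   - parametric: Tukey on the repeated-measures error, or Holm-adjusted paired contrasts;
   - rank: Holm-adjusted Wilcoxon tests, or a Friedman test before the pairwise Wilcoxon tests. One of the two is enough.
4. Reserve unadjusted paired t and Wilcoxon tests for outcomes with two moments.

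**Cost.** This needs revised analysis wording and slightly more modelling work. Within-arm p-values become somewhat less favourable. No new data are needed, and since the article reports that data are still being collected, the change can be made before analysis.

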## Background

Knee osteoarthritis (OA) is a chronic degenerative disease of an inflammatory nature that is characterized by changes in the articular cartilage, the presence of fibrillation areas, and cracking and thickening of the subchondral bone. Clinically, it is associated with pain, stiffness, deformity, and loss of functional capacity [1, 2]. Approximately 10% of the population over the age of 60 years is affected by OA; 80% of this population have movement restrictions, and 25% have functional limitations that compromise the performance of daily activities [3, 4].

Exercise is one of the therapeutic strategies that helps to minimize the deleterious effects on the musculoskeletal system generated by aging while preserving independence; promoting weight control; and improving or maintaining quality of life, functional capacity, and emotional well-being [5, 6]. However, the practice of exercises performed on the ground can aggravate joint pain and increase the risk of falls in this population [7, 8].

Aquatic physiotherapy is considered a safe and effective tool in the treatment of knee OA because immersion in hot water decreases the joint overload and pain symptoms and improves functional capacity and quality of life [9–11]. On the basis of these assumptions, the following hypothesis was formulated: Aquatic physical therapy programs contribute to the increase in the pain threshold, improved functional capacity, and improved quality of life in older adults with knee OA. The objective of the study is to verify the effects of an aquatic physiotherapy program on the perception of pain, functional capacity, and quality of life in older people with knee OA.

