### Procedures

#### World Health Organization Quality of Life Scale abbreviated version

The World Health Organization Quality of Life Scale abbreviated version (WHOQOL-BREF) is an instrument that has four domains: physical, psychological, social, and environmental. The WHOQOL-BREF comprises 26 questions, 2 of which are centered on the general quality of life, and the remaining 24 of which cover other facets of the instrument [18].

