#### Western Ontario and McMaster Universities Osteoarthritis Index

The Western Ontario and McMaster Universities Osteoarthritis Index (WOMAC) is a specific and reliable instrument for individuals with knee OA. This questionnaire consists of three domains: section A - pain (5 questions), section B - joint stiffness (2 questions), and section C - physical function (17 questions). The questions should be answered according to the subject’s perception of pain, joint stiffness, and level of physical function within the last 72 h. The WOMAC scores are presented on a Likert scale in which each question receives a score ranging from 0 to 100, distributed as follows: none = 0, light = 25, moderate = 50, severe = 75, and extreme = 100. The results will be determined from the sum of points of each question and divided by the number of domain questions. In this way, the final three scores will be obtained, one for each domain [19, 20].

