### Pain perception assessment

A dolorimeter (Palpeter®; Sunstar Suisse, Etoy, Switzerland), in the form of 1 kg, and a visual analogue scale (VAS) will be used. The dolorimeter consists of a plastic casing with a retractable, cylindrical aluminum ferrule 10 mm in diameter. The examiner should hold the plastic casing with the thumb and third finger by placing the index finger on the instrument orifice. Thus, the pressure exerted will be maintained for 3 seconds on each of the four previously defined anatomical points: (a) lateral joint interline, (b) medial joint interline, (c) medial condyle of the femur, and (d) the lateral condyle of the femur. Then, the volunteers should be classified for pain intensity according to VAS. This consists of a 10-cm line containing numbers ranging from 0 to 10, where 0 represents “no pain” and 10 represents “worst possible pain” [21].

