### Timed Up and Go test

The Timed Up and Go (TUG) test protocol comprises the following sequence of movements: rising from a chair, walking 3 m, turning around, and sitting back down in the chair. The time it takes the subject to perform this sequence of movements is recorded [22]. The best time of three attempts is taken into consideration.

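### Thirteen outcome scores share an unadjusted 0.05 threshold and none is named primary: about 49% chance of a false difference in either direction, about 28% favouring the intervention

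*Protocol article*

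**What the plan says.** The Analysis section of the protocol article sets one rule for every test: "In all tests, results will be judged to be statistically significant when α values are <0.05". The tests include Student's t "test for independent samples to compare the groups and two paired samples to compare the times", with Mann-Whitney and Wilcoxon tests for nonparametric data. There is also a repeated-measures analysis of variance with a Tukey post hoc test. No order or adjustment across outcomes is given.

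The Background states the aim as "to verify the effects of an aquatic physiotherapy program on the perception of pain, functional capacity, and quality of life in older people with knee" osteoarthritis, with the three constructs side by side. The scores behind them are:

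- Pain VAS under dolorimeter pressure: "the pressure exerted will be maintained for 3 seconds on each of the four previously defined anatomical points". No rule for combining the points is given.
- WOMAC: "the final three scores will be obtained, one for each domain". There is no total score.
- WHOQOL-BREF: it "is an instrument that has four domains: physical, psychological, social, and environmental", plus two general items.
- TUG: "The best time of three attempts is taken into consideration", so one score.
- Sit-and-reach: one score, the best of three attempts.

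The Sample size section gives an alpha, a figure of 80% labelled beta, and 15 per group. It gives no outcome, effect size or standard deviation.

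**The concern.** Nothing in the article says which result decides the trial. The objective does not rank pain, function and quality of life. The sample size cannot reveal the intended primary outcome, because it is linked to none. The Discussion lists flexibility, TUG, WOMAC and WHOQOL-BREF as expected to improve, again without ranking.

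Under the stated rule every score has equal standing. Pain alone has up to five chances: four VAS points and the WOMAC pain domain. A report could therefore rest a claim of benefit on whichever score crosses 0.05. The 5% would then describe each single test and not the error rate of the conclusion. The Tukey procedure does not help, because it compares moments or groups within one outcome and does nothing across outcomes.

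**Working it through.** **The plan's own figure.** The article states no familywise error rate, so there is none to reproduce. Its one design figure, 15 per group, can only be solved backwards. Reading the 80% as power, a two-sided t test at 0.05 with 15 per group needs a standardised difference of 1.06. No outcome is attached to such a difference, so the calculation does not point to a primary outcome.

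**Inputs**

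- Threshold: 0.05 per test (Analysis).
- Sidedness: not stated. Two-sided is assumed, so a false result in the favourable direction has probability 0.025 per test.
- Number of scores: 4 VAS + 3 WOMAC + 4 WHOQOL-BREF + 1 TUG + 1 sit-and-reach = 13. If the four VAS points become one score: 1 + 3 + 4 + 1 + 1 = 10. The two general WHOQOL-BREF items are not counted.
- One between-group test per score, and no true effect on any score.

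**Independent tests**

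- Either direction, 13 scores: 1 − 0.95^13 = 0.487
- Favouring the intervention, 13 scores: 1 − 0.975^13 = 0.280
- Either direction, 10 scores: 1 − 0.95^10 = 0.401
- Favouring the intervention, 10 scores: 1 − 0.975^10 = 0.224
- Five pain scores alone: 1 − 0.95^5 = 0.226 in either direction, and 1 − 0.975^5 = 0.119 in favour

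**Correlated tests.** The article gives no correlations, so a range is shown. For 13 normal test statistics with common correlation ρ and c = 1.96:

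- Either direction: 1 − ∫ φ(u) [Φ((c − √ρ·u)/√(1−ρ)) − Φ((−c − √ρ·u)/√(1−ρ))]^13 du
- In favour: 1 − ∫ φ(u) [Φ((c − √ρ·u)/√(1−ρ))]^13 du

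| ρ | Either direction | Favouring the intervention |
|---|---|---|
| 0 | 48.7% | 28.0% |
| 0.3 | 41.8% | 21.4% |
| 0.5 | 33.4% | 16.7% |
| 0.7 | 24.1% | 12.0% |

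**Bounds under any dependence (Bonferroni).** 13 × 0.05 = 65% in either direction; 13 × 0.025 = 32.5% in favour.

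**What is not counted.** The Analysis section also applies 0.05 to comparisons over time within each arm. With one pre-post comparison per score, that is 13 × 2 = 26 further tests. The section on intervention and follow-up names both M2 and M3 after the initial evaluation but does not make clear what is measured at each. Testing at both would add more. None of this enters the figures above.

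**Comparison.** One two-sided test at 0.05 carries a 2.5% chance of a false benefit. The stated rule raises this by a factor of 28.0/2.5 = 11.2 under independence, and 16.7/2.5 = 6.7 at ρ = 0.5.

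**The case against.** The strongest reply has three parts.

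First, no sentence says the trial succeeds if any single score is significant. The Background hypothesis joins pain threshold, functional capacity and quality of life, and the Discussion expects several measures to improve together. Requiring all three constructs would not inflate error across them. This stands as a limit on certainty: selective claiming is allowed by the rule but not prescribed. It does not remove the problem. The joint hypothesis is never turned into a decision rule, and several scores remain within each construct.

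Second, the registry entry, the SPIRIT checklist and the figures are cited but not shown, and any of them might name a primary outcome. Multiplicity handling is also often left to a statistical analysis plan. This stands to the extent that the registry must be checked first. But the article does more than stay silent: it fixes one threshold for all tests, and following it as written inflates the error.

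Third, the count of 13 assumes that the VAS points are analysed separately, which the article does not settle. This stands, and is why the 10-score figures are given.

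A reader might also infer from 1 − 0.95^13 that there is up to a 49% chance of a falsely significant benefit. The article does not support that. The 49% covers both directions. It would be a benefit probability only if every test were one-sided at 0.05, which is not stated. Nor is it a maximum: it is the independence value. It also exceeds the 32.5% upper bound for a false benefit from 13 two-sided tests.

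**Conclusion.** The defect is real and should be corrected before analysis. The article applies an unadjusted 0.05 to every test and names no primary outcome. With no true effect, the chance of at least one significant group difference is about 49% in either direction and about 28% in favour of the intervention (40% and 22% if the VAS points are combined).

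These figures assume independent, two-sided between-group tests, one per score. Positive correlation, which is likely among pain and function scores, lowers the 13-score figures to about 42% and 21% at ρ = 0.3, and to 33% and 17% at ρ = 0.5. Within-arm tests or a second post-baseline moment would raise them. Even the 17% is several times the 2.5% of a single test, so the conclusion does not depend on independence.

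**What to change.** 1. Check whether the registry entry already names a primary outcome. If it does, use it and say so in the analysis wording.
2. If it does not, write a dated note before any analysis naming one primary outcome and one time point. Examples are WOMAC pain, or a single pre-specified summary of the four VAS points, at the end-of-intervention assessment.
3. Base the trial's main conclusion on the between-group test of that outcome at 0.05. The false-positive rate of that conclusion is then 5%, or 2.5% in the favourable direction.
4. Treat all other outcomes as secondary. Either control them by a fixed order or Holm's method, or report them as estimates with 95% confidence intervals and no significance claims.

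The cost is a protocol or registry note and a change to the Analysis wording, with no extra participants or measurements. The downside is that secondary outcomes no longer support stand-alone claims. The Trial status section says data are still being collected, so the choice can still be made before analysis. Because the trial is open, the note should be dated so that readers can see it preceded the results.
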